### Biological Interpretation

Biological interpretation follows standard criteria [ACMG recommendations (Richards et al., 2015; Riggs et al., 2020)]. Briefly, balanced and imbalanced SV and SNV/Indel/Small exonic deletions, or duplications are all performed by two independent biologists. All variations are checked on. bam data and doubtful variations are confirmed using standard molecular analysis before biological analysis (less than 10 mutated reads for SNV, doubtful *de novo* status, doubtful deletion, duplication or translocation/inversion … ).

For CNV (duplication, deletion), current cytogenetic analysis is performed based on DGV, inheritance mode, recurrency, and gene contents. For balanced SV, only variations disrupting a known ID gene are retained for interpretation. Small SNV/indel are analyzed following mendelian modes of transmission (*de novo* AD or X linked variations, transmitted AD variation in case of known incomplete penetrance or suspected parental mosaic, maternally X transmission in male patients, homozygous or compound heterozygous variations (SNV or CNV) in autosomal recessive hypothesis). This broad approach ensures that co-occurring mutations (expected in about 5% of cases) will be identified (Yang et al., 2014).

Variants of interest are then recorded in the e-CRF and discussed during the MDM.

#### Multidisciplinary Meeting

Each MDM includes clinician geneticists from the recruiting center, clinicians in charge of the patients’ follow-up (i.e., neuropediatricians, neurologists, pediatricians, etc.), molecular and chromosomal geneticists (from the reference laboratory and its mirror laboratory). To ensure a reasonable number of cases to be reviewed by each MDM, three independent MDMs are organized in parallel, each of them grouping two laboratories and four clinical centers. Each MDM will thus review about 400 inclusions. In order to ensure consistency in decision-making between MDMs, all positive cases from the three MDMs will be validated in a general DEFIDIAG study review meeting.

Each MDM is organized according to the following format: discussion of the list of variants of interest obtained by the simplex 44GPS analysis; then by GSS analysis (for the 196 randomized patients); and finally, by GST. At each step, additional confirmation analysis that would be required in the course of standard care (Sanger, qPCR, FISH, analysis on mRNA, etc.) is recorded on the MDM report and in the e-CRF, for further medico-economic evaluation. The final conclusion concerning the pathogenicity of variant(s) identified by the different approaches will be reached during the session and recorded in the e-CRF MDM conclusion. If additional confirmation methods are required, the reference laboratory will be in charge of this analysis and the case will subsequently be reviewed in a future MDM. The final results are recorded in a research report communicated to the clinical geneticist who included the index case.

Candidate genes or variations (new genes, or putative variations with no obvious pathogenic effect in known genes) are classified as class 3, of unknown significance until the end of the project. Potential reclassification will be managed using standard care procedures such as splice effect, epigenetic signature, functional studies, and cohorts of patients using international collaboration.

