Specifically, the primary objective of this study is to compare the percentage of causal genetic diagnosis identified by GS performed on a trio (the patient and both parents) (GST), to the use of the current French reference minimal strategy (Fragile X + CMA + 44GPS) in ID patients attending a first genetics consultation. Secondary objectives focus on the diagnostic yield, and include the following:• To compare the percentage of ID causal diagnosis identified by GST, to GS in the proband only (i.e., genome in solo, GSS) in a subgroup of randomized patients attending for a first genetic investigation. This evaluation is useful because in genetic counseling, both parents are not always available.• To describe the estimated additional diagnostic yield that would be obtained at each step in sequential analysis of the GS data: for the minimal 44GPS gene panel, the list of genes known to be associated with disease from OMIM (referred to simply as OMIM), and ES, in patients attending for a first investigation (never-explored patients) and in patients who have already undergone investigations (previously-explored patients).• To compare the percentage of causal diagnosis of ID identified by GST to that obtained with the French reference minimal strategy in various subgroups (defined according to age, severity of ID, presence of major non-cerebral manifestations or epilepsy), for patients with ID attending for a first genetic investigation (never-explored patients).• To compare the percentage of causal structural changes (CNV, balanced structural variants) identified by GST versus CMA.• The DEFIDAG study also aims to compare the reference strategy, GST and GSs, in terms of costs and effectiveness for the causal diagnosis of ID in patients with ID of unknown etiology, attending for a first genetic investigation.• Finally, three impact studies are planned. The first will estimate the costs associated with searching for a molecular diagnosis that could potentially be avoided by performing GS as the first line approach. The second will evaluate the impact on the frequency and type of medical, medico-social and psychological care in the year following the release of GS results, compared to care during the year prior to inclusion, in particular in patients who were already engaged in a diagnostic process prior to being invited to participate in the DEFIDIAG study. The third impact study will be performed in two centers, and will use a qualitative approach, namely interviews with a sample of parents, to explore: 1) the burden experienced by the parents, 2) emotional adjustment of the patient and the parents to the results of genetic tests, and 3) the patient and parents’ perception of the future.

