GST analysis is performed following a harmonized, consensus protocol adopted by the six clinical laboratories involved in this study, and using a common web interface (Polyweb.fr, developed in-house at the Genetic diseases IMAGINE Institute, Paris, France). All genomic variations are called by standard callers (GATK and BWA) and are subsequently ranked using several factors to facilitate analysis (protein impact, inheritance model, ID known gene and control data bases, splice prediction effect … ) in the Polyweb interface. For the SNV/small indel, the scheme contains a first minimal filtration step (for SNV/indel, elimination of the variations with over 1,000 hits in GnomAD, or 5 hits at homozygous state). All variations with a predicted protein impact are ranked at the top of the list and will be studied even when a first deleterious causative variation is detected. This broad approach ensures that co-occurring mutations in different genes will be identified [multi allelism is expected in about 5% of the cases (Yang et al., 2014)]. Additional bioinformatics modules such as repeat tracking, promoter and evolutionary conserved regions analysis, and mobile element insertion detection will be implemented and applied onto negative genome results during the ongoing protocol. Specific protocols for the proband GS data and 44GPS analysis are also developed and shared between the six laboratories. To limit time dedicated to GS proband analysis, SNV/indel analysis only focuses on exonic ± 20 bases of the known ID genes (SysID list) and OMIM disease-associated genes.

When the analysis is completed, variants of interest (highly suspected to be pathogenic) are recorded in a dedicated and secured electronic Case Report Form (e-CRF). Variant class (pathogenic as class 5 variant, probably pathogenic as class 4 variant or of unknown significance but highly suspected to be pathogenic as class 3 + variant) is validated during a Multi-Disciplinary Meeting (MDM) before being communicated to the patient.

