The results of the microarray analysis and Fragile X analysis will be communicated to families and collected in the dedicated e-CRF by the recruiting genetic team as soon as the results are obtained from the diagnostic laboratories. The laboratories in charge of the GS analyses will remain blinded to these results. The GS results will be available approximately 6–9 months after inclusion in the study. In the event of an emergency (such as pregnancy), the blinding can be lifted and the results delivered to families as soon as they become available.

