### Study Endpoint

#### Primary Outcome

The primary study endpoint is the identification of a causal diagnosis of ID, defined as the identification of one or more class 4 or 5 variant(s) that explain the symptoms presented by the patient, and validated during a specific MDM.

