The strategy based on GST is expected to yield a diagnosis in at least 60% of patients with ID versus 30% with the reference minimal strategy in the population of patients attending for a first genetic investigation (never-explored patients). However, the strategies will be compared in 7 subgroups: 1) 3 defined by age: children <2 years old/2–5 years/>5 years; 2) 4 subgroups of patients defined according the severity of ID, and/or 3) with associated manifestations:1) mild ID associated with another sign, 2) moderate to severe ID, 3) ID with major non-cerebral abnormality, and 4) ID associated with epilepsy The smallest sub-group (subjects with mild ID associated with another significant sign) should represent around 15% of the total population, and the difference between the GST and the reference strategy in this particular subgroup can be assumed to be less than 15%. In addition, it is assumed that fewer than 1% of diagnoses identified with the referral minimal strategy will not be identified by the GST. Finally, we will also compare GST and GSS in a subgroup of randomized patients referred for the first time. For this specific comparison, a difference of 7% is expected, and <0.1% of diagnoses identified by GSS and not by GST. Considering these 9 planned comparisons (8 comparisons between GST and the reference strategy and 1 between GST and GS), the one-sided alpha risk is fixed at 0.00278. Based on these hypotheses, and a power of 80%, among patients seen for a first genetic investigation (50% of the population to be recruited), 41 patients are required for the main comparison, and 91 patients with mild ID + other syndrome are necessary. To recruit this number of patients, we estimate that it will be necessary to screen 607 patients attending for a first referral. A subgroup of 196 patients will be randomized to undergo GSS in addition to GST plus the reference minimal strategy. The sample size for this subgroup will be sufficient to compare GST and GSS in terms of diagnostic yield, as well as in terms of efficiency (a sample size over 150 is usually deemed sufficient). As we intend to include 50% of patients attending for a first genetics evaluation (never-explored patients), and 50% of patients who have already been investigated (previously-explored patients), a total of 1,214 patients are necessary. Considering that approximately 5% of samples will not be analyzable, it will therefore be necessary to include 1,275 index cases plus both their parents, for a total of 3,825 participants.

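### No lock on the solo (GSS) and 44-gene panel class before the trio (GST) list is opened is stated, so parental information can enter the solo yield

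*Protocol article*

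**What the plan says.** - **Endpoint.** Primary Outcome counts class 4 or 5 variants "that explain the symptoms presented by the patient, and validated during a specific MDM". The yield of every strategy is thus settled at the MDM, not in the laboratory.
- **Laboratory reading.** Under Strategies Compared, two mirror laboratories read blind. One has the trio; the other reads the panel and, in randomized patients, the solo genome, both without parental inheritance. Lists may include class 3+ variants, that is, uncertain but strongly suspected.
- **Interpretation.** Biological Interpretation uses inheritance: de novo or transmitted status for SNV/indels, and inheritance mode for CNVs.
- **Meeting.** Molecular and cytogenetic staff of both laboratories attend. The panel list is discussed first, "then by GSS analysis (for the 196 randomized patients); and finally, by GST". The item recorded at each step is the confirmation testing that standard care would need, for the economic evaluation. On the class, the text says "The final conclusion concerning the pathogenicity of variant(s) identified by the different approaches will be reached during the session", with entry in the e-CRF as the MDM conclusion.
- **Return cases.** If confirmation is needed, the reference (trio) laboratory does it and the case goes to a later MDM. All positive cases also pass a general review meeting.
- **Purpose.** The Introduction justifies the trio-solo comparison thus: "This evaluation is useful because in genetic counseling, both parents are not always available". Medico-Economic Evaluation takes each strategy's diagnostic yield as its efficacy measure.

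**The concern.** The blinding between laboratories is not visibly carried through to the point where the endpoint is set. Suppose solo lists a variant that, without parents, can only be class 3+. The trio then shows it to be de novo, and the MDM concludes class 4 or 5. If that single conclusion is attached to the variant, solo is credited with a diagnosis it could not have made alone. The question would shift from whether solo can make the call without parents to whether solo listed the variant. That does not serve the stated purpose, which is the situation where parents are unavailable.

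The same yield feeds the incremental cost-effectiveness ratios, which are estimated in the same 196 patients. The route is also open for the panel, which is likewise read without parental data.

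**Working it through.** **1. Where parental information can enter**

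| Stage | Parental data available? | Is a strategy-specific class stated to be recorded? |
|---|---|---|
| Panel and solo reading in the mirror laboratory | No | Variants of interest are entered in the e-CRF, but the class is validated later at the MDM |
| MDM, panel and solo steps | List not yet opened, but the trio laboratory is in the room | No; only confirmation testing is named |
| MDM, trio step and conclusion | Yes | One MDM conclusion covering variants from all approaches |
| Later MDM after confirmation | Yes, the trio has been discussed | No |
| General review of positive cases | Yes | No |

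The third row depends on when in the session the conclusion is drawn, which the text leaves open. The fourth row does not.

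**2. Reproducing the plan's figures**

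Inputs from Population: "the one-sided alpha risk is fixed at 0.00278", nine comparisons, 80% power, an expected trio-solo difference of 7 points, fewer than 0.1% solo-only diagnoses, n = 196. The test is McNemar (Statistical Analyses).

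- Alpha: 0.025 / 9 = 0.00278, as stated.
- Let p10 be the trio-only share and p01 the solo-only share, with pd = p10 + p01 and d = p10 − p01. For a 7-point difference with p01 = 0.001: p10 = 0.071, pd = 0.072, d = 0.070.
- z(1 − 0.00278) = 2.773 and z(0.80) = 0.842.
- n = [2.773·√pd + 0.842·√(pd − d²)]² / d² = [2.773 × 0.2683 + 0.842 × 0.2590]² / 0.0049 ≈ 189. With p10 = 0.070 it is 192.
- The simpler form (2.773 + 0.842)²·pd / d² gives 192, or 195 with p10 = 0.070. The stated 196 is reproduced to within a few patients.
- The exact conditional test needs 169. It also returns the stated 41 (cells 31%/1%) and 91 (cells 16%/1%).

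**3. How few patients carry the comparison**

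Expected trio-only patients: 196 × 0.071 = 13.9, about 14. Under the exact test at least 9 discordant pairs, all in one direction, are needed, because 0.5⁹ = 0.00195 is below 0.00278 while 0.5⁸ = 0.0039 is not.

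**4. Effect of re-crediting**

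Let s be the share of trio-only diagnoses credited to solo. The documents give no value, so s is an assumed range. Then p10 = 0.071·(1 − s), with p01 held at 0.001. Asymptotic power is Φ{[d·√196 − 2.773·√pd] / √(pd − d²)}.

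Worked case, s = 0.25: p10 = 0.05325, pd = 0.05425, d = 0.05225. The numerator is 0.7315 − 0.6458 = 0.0857; divided by 0.2270 this is 0.378, and Φ(0.378) = 65%.

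| s | Patients moved | Difference (points) | Power, asymptotic | Power, exact |
|---|---|---|---|---|
| 0% | 0 | 7.0 | 82% | 90% |
| 10% | 1.4 | 6.3 | 76% | 83% |
| 25% | 3.5 | 5.2 | 65% | 65% |
| 50% | 7.0 | about 3.5 | 40% | 22.5% |

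**5. Trio against the reference strategy**

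With 607 first-investigation patients and 1% reference-only diagnoses, power stays near 100% even if the 30-point difference falls to 10. The mild-ID subgroup is more sensitive: at n = 91, exact power is 80% at 15 points, 59% at 12 and 41% at 10.

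**The case against.** The strongest reply is that the text never says the class is set after the trio is shown. The fixed order of panel, solo, trio looks like a deliberate safeguard and is compatible with a decision at each step. A journal article may leave the e-CRF fields and meeting rules to the full protocol. This stands against any claim that solo variants are classified only after trio disclosure, which a reader might infer. It does not remove the point. The meeting format is described in some detail, including what is recorded at each step, and a class is not among those items. The order protects the comparison only if the class is fixed before the next list opens, and the later MDM follows trio discussion on any reading.

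Other replies, and what stands of them:

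- **Direction.** A reader might infer a certain bias towards zero. A variant found to be inherited from an unaffected parent could be downgraded, which would lower solo yield and widen the difference. The bias is also bounded, since a variant that solo never listed cannot be re-credited. Shrinkage is likely, not certain.
- **Legitimate parental testing.** Confirmation in parents might be part of care after a solo result. The article does not settle this; any such test should be counted and costed under solo.
- **Search space.** One might call the narrower solo search a second distortion. The article says "To limit time dedicated to GS proband analysis, SNV/indel analysis only focuses on exonic" and a short flank in known ID and OMIM disease genes. That limit covers SNV/indels only, is a stated choice with a stated reason, and is part of what solo means here.
- **CMA and Fragile X.** They are absent from the listed MDM steps, so one might infer that the reference strategy is judged by a different standard and want them opened first. Silence does not establish that. Strategies Compared says "The results of the microarray analysis and Fragile X analysis will be communicated to families and collected in the dedicated e-CRF" by the recruiting team and keeps the genome laboratories blinded to them. Opening them at the MDM before the trio would break that blinding.

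**Conclusion.** The concern holds as a gap in how the endpoint is fixed, not as a demonstrated bias. One meeting decides the class for all strategies, inheritance informs that class, no step-specific lock is stated, and return cases are reviewed with the trio known. Parental information can therefore reach the solo and panel yields.

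The size cannot be computed from the article. The power losses in the table rest on assumed re-credited shares, on the plan's 7-point difference and on 0.1% solo-only diagnoses. What they establish is fragility: moving three or four patients brings power to about 65%. The damage falls on the trio-solo comparison and on the cost-effectiveness analysis. The documents do not support extending it to the main trio-reference comparison, which is robust.

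**What to change.** 1. At each MDM step, record in the e-CRF and lock the class of each panel variant, then of each solo variant, before the next list is opened. Use only that strategy's own data, plus any confirmatory test that strategy would itself order, with its cost.
2. Carry this class unchanged through later MDMs and the general review, except for the results of those tests. State whether parental testing counts among them.
3. Use the locked class for each strategy's yield and for the cost-effectiveness analysis. Keep the final class for a secondary analysis.
4. For cases already discussed in the 196-patient subgroup, re-derive the solo class with inheritance evidence removed.
5. Optionally, report the trio-solo difference also within the SNV/indel search space common to both.

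The cost is a few e-CRF fields, a few minutes per case and a desk re-classification. The last is imperfect if those doing it know the trio result. Locking may also reveal solo calls that the trio later overturns. These would count as solo-only diagnoses, planned at under 0.1%, and the final-class analysis would identify them. Trial Status gives 955 inclusions of a planned 1,275, with genome results following some months later, so at that date many sessions could still have been handled prospectively.

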#### GS Results Visit and Subsequent 12 months Follow-Up

When the results become available, and regardless of the results (positive or negative), the clinical geneticist who included the patient (and parents) will inform patient/family about the results of the GS during a dedicated visit. These results will be made available approximately 9 months after inclusion in the study. If the study identifies one or several class 3+, 4, or 5 variation(s), the clinical geneticist will explain the type of associated medical condition, its mode of inheritance and the risk of recurrence for a future pregnancy, as well as the modalities of care. All information (examinations, medical or non-medical treatment, medico-social follow-up, etc.) will be collected by the geneticist, assisted by a CRT. The diary kept by the families will be retrieved and integrated into the e-CRF. A new diary will be given to the family for the subsequent 12 months, and the phone contact by the CRT is planned. If the parents or adult with mild ID agreed to participate in the qualitative study, the sociologist/psychologist will then contact them to check that they all still agree to continue the interviews and organize the second interview.

Twelve months after the GS results are made known to the patient, a final visit at the hospital will be organized (this visit can be replaced by a telephone contact, if necessary) to assess the medical condition, collect any results and retrieve the diary. If the parents agreed to participate in the qualitative study, once again, the sociologist/psychologist will then contact them to check that they all still agree to continue the interviews and organize the third interview.

### Medico-Economic Evaluation

A cost-effectiveness analysis will be conducted over the estimated 9–12 months (maximum) required to perform the GS, interpret the data and return the results to the patient. Efficacy will correspond to the diagnostic yield of each of the three strategies being compared. In order to estimate costs from the perspective of the health service, patient management will be divided into three main periods of healthcare consumption (Figure 2). The costs in the medico-economic evaluation will be direct costs, corresponding to medical procedures carried out during period 2. They will include: 1) the costs of consultation with the clinical geneticist in the recruitment centers, 2) the costs of exams preceding the genetic analysis and inclusion in the DEFIDIAG project, and the cost associated with the first blood sample and its transport, 3) the costs associated with any new blood draws required; 4) the costs of genetic analyses, and 5) the costs of any additional and confirmatory tests. Most of these procedures will be valued using social security prices, except for GSS and GST, which will be valued using a micro-costing method (Drummond et al., 2005).

